#### Strategies to improve adherence to interventions {11c}

A clinical research nurse will organize outpatient visits and follow-up with participants in this research. Patients will get text messages reminding them of the appointment time in advance of the subsequent visits. When a patient fails to return on time, the research nurse will contact them through phone or WeChat. To further alleviate the stress on subjects, we will streamline the trial procedure to improve the efficiency of treatment.

#### Relevant concomitant care permitted or prohibited during the trial {11d}

Other therapies that could have an impact on the study’s outcomes, such as medications affecting bone metabolism or treatments which may facilitate OTM, will be prohibited during the period of the trial.

#### Provisions for post-trial care {30}

Participants will be informed that it is voluntary to be enrolled in this trial prior to the study. Subjects can refuse to participate or drop out of the study at any phase of the trial for any reason. Their medical care and rights will not be affected. We will record it faithfully. If an intervention-related adverse event happens during the trial, patients will get appropriate treatment measures for free and financial compensation after the evaluation of the expert committee.

### Outcome measures {12}

Outcome measurements will be recorded before randomization (V0), at the initiation of ER (V1) and after space closure (V2). The primary outcome is the space closing time, which can reflect the effectiveness of piezocision directly. The secondary outcomes are designed to compare the periodontal health, the alveolar bone changes, and torque control of maxillary anterior teeth before and after ER between the two groups. We will also pay attention to the patient-centered outcomes as to evaluate the surgery more comprehensively.

#### Primary outcome

The primary outcome with respect to the efficiency of piezo surgery is the space closing time (T_V2-V1_) from the initiation of ER (V1) to the end of the space closure (V2). All the subjects will be revisited every 2 weeks. An assessor blinded to groups assignment will take charge of recording each visit time and evaluate whether the extraction space has been completely closed by using dental floss to confirm the contact point of adjacent teeth.

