#### Secondary outcomes

The secondary outcomes will contain the root length, thickness of labial and palatal alveolar bone, vertical bone height (VBH), probing depth (PD) of maxillary anterior teeth, cephalometric analysis, visual analogue scale (VAS), and postoperative satisfaction questionnaire (PSQ).

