**Table 1 Tab1:**
[figure not shown]
Schedule of enrollment, interventions, and assessments (recommended by SPIRIT)

*VBH* vertical bone height, *PD* probing depth, *VAS* visual analogue scale, *PSQ* postoperative satisfaction questionnaire

^a^VAS will be filled out daily for 7 days postoperatively

^b^PSQ will only be filled out in participants of piezocision group

^c^All the subjects will be followed up every 2 weeks. The status of space closure will be monitored every visit time

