## Statistical methods

### Statistical methods for primary and secondary outcomes {20a}

All data will be analyzed by an independent statistician utilizing SPSS (Version 24.0). The data analysis set in this study will comprise of the full analysis set (FAS), per protocol (PP) set, and safety set (SS). The subjects who receive the treatment at least once after randomization and have corresponding evaluation will be analyzed as the FAS. The subjects who follow the protocol strictly and complete the follow-up will be enrolled in the PP set. SS includes the subjects who have received intervention at least once with safety assessment during the trial. The primary endpoint will be analyzed in the FAS and PP, and secondary endpoints will be analyzed in the FAS. The safety of the treatment will be analyzed in the SS.

Continuous data will be presented as the mean ± standard deviation (SD) or median (P25-P75), while categorical data will be presented as absolute frequencies (percentages). *T* test or Mann-Whitney *U* test will be used to compare primary endpoints between groups. For secondary endpoints, the *t* test or Mann-Whitney *U* test will be used to compare continuous variables between groups, and categorical variables will be analyzed by chi-square test or Fisher’s exact test. The statistical tests used in the study will be two-sided. When *P*<0.05, it will be considered statistically significant.

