### Methods for additional analyses (e.g., subgroup analyses) {20b}

No subgroup analyses or any other additional analyses will be planned in this study.

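### Space closing time depends on the distance to close, but the article describes no measurement of residual space at V1 and fixes an unadjusted test: a loss of precision, not a bias

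*Protocol article*

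**What the plan says.** Under Primary outcome, the article states: "The primary outcome with respect to the efficiency of piezo surgery is the space closing time". This is the elapsed time from V1 (start of en-masse retraction) to V2 (end of closure). At two-weekly visits a blinded assessor will "evaluate whether the extraction space has been completely closed by using dental floss to confirm the contact point of adjacent teeth", which is a yes/no judgement. Footnote c of Table 1 adds: "The status of space closure will be monitored every visit time". No distance in millimetres is described.

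Under Secondary outcomes, the list covers root length, bone thickness and height, probing depth, cephalometry and patient-reported scales. Residual extraction space is not on it. CBCT is taken at V0 and V2, not at V1.

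Under Statistical methods {20a}, a t "test or Mann-Whitney *U* test will be used to compare primary endpoints between groups". Section {20b} adds: "No subgroup analyses or any other additional analyses will be planned in this study". Together these fix an unadjusted primary comparison, so the choice is not simply left to an analysis plan that we cannot see.

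Two further points bear on starting space. Patients may have either no crowding or mild crowding (Inclusion criteria), and the arch is aligned and levelled after randomisation and before V1 (Intervention description {11a}).

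**The concern.** The stated objective is acceleration, which is a matter of speed. Closing time is distance divided by speed, so it stands in for speed only when the arms start with similar distances. Relieving crowding uses extraction space, so the space left at V1 will differ between patients.

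With 20 patients, the arms can differ by chance in mean starting space. Without a V1 reading nobody could tell whether they did, and variation that might be explained stays in the error term. By the article's own Discussion, an earlier trial fixed the period at 4 months and measured the amount of closure. Here the duration is measured, and the distance is neither fixed nor recorded in what the article describes.

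**Working it through.** **1. The plan's own figure.** Inputs from Sample size {14}: 9 v 5.4 months, so a difference of 3.6; SD 2 in each arm; alpha 0.05, two-sided per {20a}. Exact power uses the noncentral t distribution with 2n − 2 df and noncentrality 3.6 / (2 × √(2/n)).

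- n = 7 per arm: 87.0%
- n = 8 per arm: 91.7%
- Dropout: 8 / 0.8 = 10 per arm, 20 in total

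The stated 8 per arm and 20 in total reproduce. The SD of 2 is a total SD, so it already contains whatever variation starting space contributes.

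**2. Chance imbalance.** The difference in mean V1 space between arms has standard error √(2/n) in units of the between-patient SD of space.

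- n = 10: √0.2 = 0.447; P(|difference| > 0.5 SD) = 2 × [1 − Φ(0.5/0.447)] = 26%
- n = 8: √0.25 = 0.5; the same probability is 32%

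**3. What that could mean in months (assumed inputs).** The documents give neither the mean nor the spread of V1 space. Suppose about 7 mm is closed in 9 months, with time proportional to space: 9/7 = 1.29 months per mm.

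| Assumed SD of space | SD of time due to space | Share of planned variance (2² = 4) | Shift from a one-SE imbalance, n = 10 |
|---|---|---|---|
| 0.5 mm | 0.64 months | 10% | 0.29 months |
| 1.0 mm | 1.29 months | 41% | 0.57 months |

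An SD of 1.5 mm would give 1.93 months, or 93% of the planned variance. That is a correlation of 1.93/2 = 0.96, which is too close to deterministic to rely on.

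**4. Gain from adjustment.** ANCOVA with one covariate that has correlation ρ with closing time: residual SD = 2 × √(1 − ρ²), df = 2n − 3, and variance multiplied by 1 + 1/(2n − 4) for estimating the covariate effect. A 30% reduction is 0.30 × 9 = 2.7 months; the planned 40% is 3.6 months.

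| Scenario | Unadjusted | ρ = 0 | ρ = 0.3 | ρ = 0.5 | ρ = 0.7 |
|---|---|---|---|---|---|
| 30% reduction, 10 per arm | 81% | 79% | 82% | 89% | 97% |
| 30% reduction, 8 per arm | 71% | 67% | 71% | 79% | 92% |
| 40% reduction, 10 per arm | 96.7% | 95.7% | 97.1% | 98.9% | 99.9% |
| 40% reduction, 8 per arm | 91.7% | 89.1% | 91.7% | 95.8% | 99.4% |

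The ρ = 0 column shows the cost of a useless covariate: about 1 to 4 points. At 10 per arm the half-width of the 95% CI is 1.88 months unadjusted and 1.68 at ρ = 0.5. These figures take every closing time as observed and normally distributed; the 12-month value assigned to dropouts and unclosed cases under {20c} is ignored.

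**The case against.** The case for leaving the plan alone has real weight.

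- **Validity.** Randomisation makes the unadjusted comparison valid, and its confidence interval already allows for chance imbalance. This stands. A reader might infer that the omission biases the result or undermines the sample size; the documents do not support that.
- **Importance of space.** A reader might suppose that starting space is the largest predictable source of variation. No figure in the documents says so. Eligibility also narrows the spread: all patients have both maxillary first premolars extracted, and crowding is at most mild.
- **Gain at the planned effect.** At a 40% reduction, power is already high and a weak covariate adds almost nothing. This stands. The gain matters if the true effect is smaller. That is plausible, since the 40% comes from an alignment study and the Discussion calls the conclusions of two en-masse retraction trials disputed.
- **Outcome choice.** Duration was chosen deliberately and matters to patients. Adjustment keeps duration as the endpoint.
- **Timing of the covariate.** V1 space arises after randomisation and after alignment by unblinded staff. It precedes the surgery, so the surgery cannot affect it, but it is not a pre-randomisation baseline. For the same reason, failing to stratify on it is no fault: it is not known at randomisation.
- **Visibility.** The article says outcome measurements are recorded at V1, and the body of Table 1 is not shown. The point therefore concerns what the article describes.

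**Conclusion.** The point holds as a cheap improvement in precision. The article fixes an unadjusted comparison of raw duration and describes no measurement of the distance to be closed. Validity and sample size are intact.

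The one quantity that needs no assumed spread or correlation is the chance of an imbalance above 0.5 SD in starting space: about 26% at 10 per arm, taking space as roughly normal. Without a V1 reading such an imbalance would go unseen. The gain in power rests wholly on an assumed correlation: negligible at 0.3, and at 10 per arm with a 30% reduction about 8 points at 0.5 and 16 points at 0.7. At the planned effect it is at most about 3 points at 10 per arm and 8 points at 8 per arm over the same range.

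**What to change.** 1. At V1, before piezocision and before any retraction force, have the blinded assessor record residual extraction space on each side in mm with a caliper.
2. Pre-specify the sum of the two sides as the single covariate in one named primary model. If the comparison of means is kept, that model is ANCOVA. Report the unadjusted result as supportive.
3. State that V1 space is measured after randomisation and open-label alignment, so it precedes surgery but is not a pre-randomisation baseline. Report it by arm so that any imbalance is visible.

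The cost is two caliper readings at a visit that already takes place, one degree of freedom, and about 1 to 4 points of power if space turns out to be nearly unrelated to closing time. For any patient whose retraction has already begun, a direct V1 reading can no longer be obtained.

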#### Secondary outcomes

The secondary outcomes will contain the root length, thickness of labial and palatal alveolar bone, vertical bone height (VBH), probing depth (PD) of maxillary anterior teeth, cephalometric analysis, visual analogue scale (VAS), and postoperative satisfaction questionnaire (PSQ).

#### Root length

Participants will take cone beam computed tomography (CBCT) scans at V0 and V2 using KaVo 3D eXam (KaVo, Biberach, Germany). The CBCT scan data will be stored as Digital Imaging and Communications in Medicine (DICOM) files and imported into a software (OnDemand3D Application, CyberMed Corporation, Seoul, Korea) for reconstruction and measurement. The root length will be measured as the vertical distance from the cementoenamel junction (CEJ) to the root apex (Fig. 3).

**Fig. 3 Fig3:**
[figure not shown]
Measurements of the root length, labial and palatal alveolar bone thickness, and the vertical bone height of maxillary anterior teeth. Line 0 represents the long axis of the teeth and line 1 the CEJ, while line 4 is parallel to line 1 and passes through the root apex. The root length will be divided into 3 equal parts by line 2 and line 3. Meanwhile, a, b, c, d, e, and f represent the distance from the labial and palatal alveolar bone to the root surface. The VBH will be measured as the distance between the CEJ and the alveolar bone crest

#### Thickness of labial and palatal alveolar bone

Paralleled to and passing through the long axis of each examined tooth, the sagittal plane will be adjusted to be perpendicular to the labial surface of the tooth in multiplanar reconstruction image. The root length will be divided into 3 equal parts (L0 representing the long axis of the teeth; L1 representing the CEJ; L4 representing the root apex). The thickness of the labial and palatal alveolar bone of the anterior teeth will be measured from the cortical plate of the alveolar bone to the root surface (Fig. 3).

#### VBH

The VBH is defined as the perpendicular distance between the alveolar ridge crest and the CEJ, which will be measured in the same sagittal plane mentioned above (Fig. 2).

#### PD

The probing depth of maxillary anterior teeth will be measured using the electronic Florida probe (Florida Probe Cooperation, Gainesville, Florida, USA) with the controlled force of 15 g.

#### Cephalometric measurements

Preoperative and postoperative lateral radiographs of each subject will be all taken by the same X-ray machine (OC200D, Ingram, Finland). The Dolphin Software (Dolphin Imaging Software V11.7, USA) will be used for cephalometric analysis of the lateral radiographs. Cephalometric parameters are shown in Fig. 4, including SNA, an indicator reflecting the anteroposterior position of the maxillary bone relative to the cranium; MP-SN, the index reflecting the steepness of mandibular body; U1-SN, the index reflecting the inclination of maxillary anterior teeth; and UL-Ep, an indicator of the soft tissue protrusion of the upper lip.

**Fig. 4 Fig4:**
[figure not shown]
Cephalometric landmarks and indicators. *S* sella, *N* nasion, *A* subspinale, *Ui* upper incisor, *Uir* upper incisor root, *Me* menton, *Go* gonion, *UL* upper lip anterior, *MP* the mandibular plane, *Ep* the aesthetic plane, *UL-Ep* distance between UL and the aesthetic plane

#### VAS

The level of discomfort will be evaluated utilizing VAS from the day of ER initiation (V1) in both groups for successive 7 days. Briefly, we will grade the intensity of pain on a scale from 0 (no pain) to 10 (maximum pain).

#### PSQ

PSQ will be filled out on the day of surgery for subjects in PG. Patients will share their subjective perception during the surgical treatment, including the feeling of vibration, sound fear, pain, teeth ache, and teeth numbness, which will be graded on a scale from 0 (the minimum of feeling) to 5 (the maximum of feeling).

### Participant timeline {13}

The timeline of the clinical trial is shown in Table 1.

**Table 1 Tab1:**
[figure not shown]
Schedule of enrollment, interventions, and assessments (recommended by SPIRIT)

*VBH* vertical bone height, *PD* probing depth, *VAS* visual analogue scale, *PSQ* postoperative satisfaction questionnaire

^a^VAS will be filled out daily for 7 days postoperatively

^b^PSQ will only be filled out in participants of piezocision group

^c^All the subjects will be followed up every 2 weeks. The status of space closure will be monitored every visit time

### Sample size {14}

The sample size will be calculated using PASS system (version 15.0.5) in this study. According to a study reported in 2016, the mean alignment time is reduced by 40% in the intervention group compared to the control group [41]. Our anticipated hypothesis is that the overall treatment time of ER in CG is assumed to be 9 months, while in PG is 5.4 months, with standard deviation of 2 for both groups. Assuming equal variance, 8 participants in each group can provide 90% power to reject the null hypothesis. The significance level is 0.05 and the power is 90%. Considering an anticipated 20% dropout rate, the final sample size is a total of 20, and 10 participants in each group.

### Recruitment {15}

Shanghai Stomatological Hospital will serve as the primary research center for participants’ recruitment. Eligible subjects will be recruited through posters in the waiting area and recruitment ads on official website and WeChat official account of the hospital, from October 2019 to March 2022. Shanghai Stomatological Hospital comprises relevant departments involved in this study, including orthodontic department and periodontal department, with a team of medical professionals. Eligible patients from outpatient clinics will be informed by clinical physicians and contacted by clinical research coordinators (CRC) to arrange screening visits. After obtaining the informed consent, screening will be conducted, and subjects who meet all inclusion and exclusion criteria will be enrolled in the study.

## Assignment of interventions: allocation

### Sequence generation {16a}

An independent statistician will generate a random sequence of 40 sequential numbers utilizing SPSS (version 24.0).

### Concealment mechanism {16b}

Sequential numbered, opaque, sealed envelopes (SNOSE) will be used as a method of allocation concealment.

### Implementation {16c}

An independent researcher will be responsible for the enrollment of participants. After signing the ICF and screening, eligible subjects will receive SNOSE with orderly numbers according to the order of enrollment. The investigator will write down the patients’ detailed information (name, gender, age, and ID number) on the SNOSE and take out the cards immediately. The subjects’ group will be determined by the random numbers in the SNOSE. The random operator and the random date will be recorded.

## Assignment of interventions: blinding

### Who will be blinded? {17a}

Since the intervention in this RCT is a surgery treatment and setting a sham surgery may cause unnecessary harm to the participants, the medical staff and subjects cannot be blinded in this study. To minimize the bias, the outcome assessor and data statistical analyst will be blinded during the trial.

### Procedure for unblinding if needed {17b}

Since the researchers and participants in this study will not be blinded, the procedure for unblinding is not applicable in this trial.

## Data collection and management

### Plans for assessment and collection of outcomes {18a}

After randomization, participants in PG will undergo ER immediately after piezocision surgery, while the ones in CG will receive ER therapy directly. All of them will be asked to fill out the VAS for 7 successive days after ER to compare the discomfort feeling between the two groups. Subjects in PG will additionally fill in the PSQ after the surgery.

The primary outcome is the space closing time (T_V2-V1_), which will be measured from the initiation of ER (V1) till the end of the space closure (V2).CBCT will be taken at V0 and V2 to measure the root length and the thickness of the labial and palatal bone of the 6 maxillary anterior teeth. Dolphin will be used for cephalometric analysis of lateral radiographs to analyze indexes related to dental, skeletal, and soft tissue changes including U1-SN, SNA, MP-SN, and UL-E.

Study staff, including orthodontists, periodontists, clinical study nurses, CRC, assessors, and statisticians, will be trained in data management.

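### The secondary outcomes are clustered within patients, but the protocol names only two-sample tests and does not fix the randomised patient as the unit of analysis

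*Protocol article*

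**What the plan says.** All references are to the protocol article.

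- **Test.** Statistical methods for primary and secondary outcomes {20a} offers, for secondary endpoints, the t test or the Mann-Whitney U test: this "test will be used to compare continuous variables between groups". On sidedness: "The statistical tests used in the study will be two-sided". The threshold is P "<0.05, it will be considered statistically significant".
- **Other analyses.** Section {20b}: "No subgroup analyses or any other additional analyses will be planned in this study".
- **Teeth.** Section {18a} uses CBCT "to measure the root length and the thickness of the labial and palatal bone of the 6 maxillary anterior teeth".
- **Sites.** The legend to Fig. 3 gives six thickness measurements per tooth: "a, b, c, d, e, and f represent the distance from the labial and palatal alveolar bone to the root surface".
- **Vertical bone height (VBH) and probing depth (PD).** "The VBH is defined as the perpendicular distance between the alveolar ridge crest and the CEJ", read in the same plane on each tooth examined. PD is also taken on the maxillary anterior teeth. The number of probing sites is not given.
- **Days.** VAS is recorded "from the day of ER initiation (V1) in both groups for successive 7 days".
- **Randomised unit.** Patients, 1:1, 10 per group (Trial design {8}; Sample size {14}).

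The article does not say how the tooth, site or day values become one value per patient. It names no model for clustered or repeated data.

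**The concern.** A t test or Mann-Whitney test assumes independent observations. Six teeth in one mouth, six sites on one root and seven pain scores from one person are not independent. The named tests are valid on one value per patient and invalid on pooled tooth, site or day values. The text of {20a} allows either, so the validity of the comparison depends on a choice that the protocol does not record.

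This matters because the trial's objective covers safety as well as efficacy. Root length, bone thickness, VBH, PD and pain are its main measured evidence on harm and tolerability. A pooled analysis would give confidence intervals that are too narrow and P values that are too small for these outcomes.

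**Working it through.** **1. The plan's own figure.** Sample size {14} assumes 9 versus 5.4 months (difference 3.6) and SD 2, at two-sided 0.05. The two-sample t test (noncentral t) has power 0.870 at n = 7 and 0.917 at n = 8 per group, so 8 is the smallest n that reaches 90%. Allowing for 20% dropout, 8 / (1 − 0.2) = 10 per group. The stated size reproduces. It concerns space closing time, which is one value per patient, and it fixes the 10 patients per arm used below.

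**2. Inputs for the check.** From the protocol: 10 patients per arm, 6 teeth and 7 VAS days per patient, 6 × 6 = 36 thickness sites per patient, alpha 0.05 two-sided. Assumed, because the document gives no value: an exchangeable ICC of 0.1 to 0.7 within patient.

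**3. Design effect.** For m values per patient, the variance of a group mean is larger than the pooled test assumes by DE = 1 + (m − 1) × ICC. Treating the pooled test as a z test, its true type I error is about 2 × [1 − Φ(1.96 / √DE)].

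**4. Six teeth per patient, 60 pooled values per arm, no true effect.** Simulation used 20,000 trials per row.

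| ICC | DE | Effective values per arm (60 / DE) | Approximate type I error | Simulated, pooled t test | Simulated, patient means |
|---|---|---|---|---|---|
| 0.1 | 1.5 | 40 | 0.11 | 0.108 | 0.051 |
| 0.3 | 2.5 | 24 | 0.22 | 0.217 | 0.049 |
| 0.5 | 3.5 | 17 | 0.29 | 0.307 | 0.051 |
| 0.7 | 4.5 | 13 | 0.36 | 0.370 | 0.052 |

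Formula and simulation agree closely. With 8 completers per arm, the pooled rates are almost the same (0.106, 0.224, 0.301, 0.375).

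**5. Other repeated outcomes, 10 per arm, same ICC values.** Pooling seven VAS days gives 0.13, 0.25, 0.34 and 0.41. Pooling all 36 thickness sites gives 0.36, 0.56, 0.65 and 0.71. The 36-site figures are the least secure, because a single common correlation across teeth and sites is a crude assumption.

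The simulation used the t test. The Mann-Whitney test makes the same independence assumption but was not simulated.

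**The case against.** The strongest reply is that {20a} can be read correctly as it stands. Its analysis sets are sets of subjects, secondary endpoints are analysed in the full analysis set, and comparisons are between the two groups. Averaging within patient and then running the named test fits that wording and holds the 5% level. An article also condenses, and the summary measure may be set out in an analysis plan not shown. Much of this stands: nothing in the document says that 60 values per arm will be compared. What remains is that the article goes beyond silence. It names the method and rules out additional analyses, and that method is sound for only some of the ways the collected data could be entered.

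A reader might infer more than the text supports:

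- **That the plan commits to dozens of tests.** Testing every tooth, site and day separately would give 6 (root length) + 36 (thickness) + 6 (VBH) + 6 (PD) + 4 (cephalometric) + 7 (VAS) = 65 tests. The document states no such number and no such intention. The count also assumes one VBH and one PD value per tooth.
- **That separate tests also give intervals that are too narrow.** They do not. Each keeps its own 5% level. Unadjusted testing of secondary outcomes that carry no confirmatory claim is largely a matter of preference.
- **That the upper end of the error range applies.** The abstract describes the CBCT endpoints as changes. Stable differences between patients cancel in a change score, so the ICC may be near the low end.

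**Conclusion.** The point holds in a conditional form. For clustered and repeated secondary outcomes, the protocol prescribes tests that need one independent value per patient and does not fix the patient as the unit. If tooth values are pooled, type I error rises from 5% to between about 11% and 37% for 10 patients × 6 teeth per arm. That range rests on an assumed exchangeable ICC of 0.1 to 0.7, which the document cannot narrow. If one value per patient is used, there is no inflation.

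The document does not show which will be done, so it cannot be said that the secondary results will be wrong. Space closing time and the four cephalometric indices are single values per patient and are not affected. This is a low-cost improvement worth making before analysis, and it does not threaten the main conclusion.

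**What to change.** Add to {20a} that the randomised patient is the unit of analysis. Then, for each tooth-level or daily outcome, pre-specify one of these:

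- **A patient-level summary:** the mean over the six teeth for root length, thickness, VBH and PD; the 7-day mean or area under the curve for VAS. For thickness, state how sites a to f are combined. Separate labial and palatal means would keep a loss on one side from being masked by a gain on the other.
- **A linear mixed model:** a random patient intercept, with tooth or day as a fixed effect.

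In either case, adjust for the V0 value where one is collected, as it is for the CBCT measures. Report one between-group difference with a 95% confidence interval per outcome, and present per-tooth, per-site and per-day results as descriptive.

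The cost is wording only. No new data or visits are needed, and both options can be run in SPSS. The downside is losing nominal tooth-level precision, which is overstated whenever values within a patient are positively correlated.
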